## Abstract

**Background:**

Pulmonary arterial hypertension (PAH) is a progressive disease characterized by high mean pulmonary arterial pressure (≥ 20 mmHg) and remodeling of the vascular arteries. Approved therapies improve symptoms and delay clinical worsening in the long term, but they do not relieve acute exertional symptoms. RT234, a drug/device combination (Respira Therapeutics, Palo Alto, CA, USA) that delivers the phosphodiesterase 5 inhibitor vardenafil to the lungs via inhalation, has been shown to reduce pulmonary vascular resistance in patients with PAH. This study aims to evaluate whether RT234 can increase oxygen capacity during cardiopulmonary exercise testing (CPET) in patients with PAH.

**Methods:**

This prospective, multi-center, open-label, two-cohort, dose-escalation, phase IIb trial in patients with PAH will evaluate the safety and efficacy of RT234 in improving exercise parameters. The trial began in September 2020 and is expected to be completed by early 2024. Patients eligible for enrollment will have a right heart catheterization–confirmed diagnosis of PAH, a 6-minute walking distance of ≥ 150 m, a minute ventilation/carbon dioxide production slope of ≥ 36, and will be on up to three stable oral and/or inhaled (not parenteral) PAH-specific background therapies. The estimated sample size is 86 patients, who will be divided into two dose cohorts. Cohort 1 will receive 0.5 mg RT234, and cohort 2 will receive 1.0 mg RT234. Each cohort will contain two subgroups based on the number of PAH background medications (up to two vs three). The trial will assess patients’ changes from baseline in peak oxygen consumption (VO_2_) during CPET 30 minutes after a single dose of 0.5 mg or 1.0 mg RT234, the change in the 6-minute walking distance, and the pharmacokinetics and safety profile of single doses of RT234.

**Conclusion:**

This is the first trial involving an as-needed medication for PAH. The trial will provide insights into the safety and efficacy of as-needed RT234 in treating the acute symptoms of PAH during exercise and will inform the design of further trials.

*Trial registration number:* ClinicalTrials.gov identifier NCT04266197.

## Background

Pulmonary hypertension (PH) is a rare disease defined by abnormally high pulmonary arterial pressure and pulmonary vascular resistance [1, 2]. Group 1 PH, pulmonary arterial hypertension (PAH) [3], is a progressive disease characterized by a mean pulmonary artery pressure ≥ 20 mmHg, pulmonary capillary wedge pressure ≤ 15 mmHg, and pulmonary vascular resistance of ≥ 3 Wood units [4], as well as physiological changes to the pulmonary arteries [5]. As the disease progresses, exercise capacity declines and daily activities become more difficult [6].

There is currently no cure for PAH. The disease is managed by approved treatments, such as endothelin receptor agonists, phosphodiesterase 5 inhibitors (PDE5i), and prostacyclin analogs that reduce symptoms and slow disease progression over time [7]. Managing the acute symptoms induced by daily activities is an ongoing challenge for patients living with PAH [8, 9] because none of the approved treatments can be used for acute symptom relief. There is therefore an unmet clinical need for an as-needed (PRN) treatment for PAH that will reduce acute symptoms and allow patients to perform daily activities and exercise.

Vardenafil is a PDE5i that has been shown to improve exercise capacity in patients with PAH [10]. Vardenafil has a slow dissociation rate (*K*_D_ 0.38 ± 0.07) [11] and rapid clearance (56 L h^–1^) [12], making it ideally suited to PRN use. An inhalable, powdered form of vardenafil has recently been developed, which is delivered via RT234 (Respira Therapeutics, Palo Alto, CA, USA), a drug/device combination product comprising powdered vardenafil hydrochloride and the Axial Oscillating Sphere Dry Powder Inhaler™ (DPI; Plastiape S.p.A., Osnago, Italy (Fig. 1)). A phase I study, RT234-CL101, has been completed for RT234 [13], which compared the pharmacokinetic (PK) profiles of RT234 and oral vardenafil in healthy volunteers. The maximum concentration (C_max_) of vardenafil was reached rapidly (time to C_max_ [T_max_] = 2 minutes), there were no serious treatment-emergent adverse events (TEAEs), and the drug was well tolerated.

**Fig. 1 Fig1:**
[figure not shown]
The Axial Oscillating Sphere (AOS) Dry Powder Inhaler (DPI) for inhalation of vardenafil. RT234 is a combination of vardenafil in powder form and the AOS DPI™ (Plastiape S.p.A., Osnago, Italy). Image copyright of Respira Therapeutics

RT234-CL202 is a phase IIb study that will investigate acute changes in exercise capacity and exertional symptoms, as assessed by cardiopulmonary exercise testing (CPET) and the 6-minute walking test (6MWT), following RT234 dosing in patients with PAH on stable, disease-specific background therapy. The study will evaluate the acute effect of single doses of 0.5 mg and 1.0 mg RT234 on CPET parameters and the change in 6-minute walking distance (6MWD) in two sequential cohorts. The adverse event profile and acute physical and cardiac effects of RT234 will be determined, as well as the PK parameters of vardenafil and the relationship between vardenafil exposure and changes in CPET parameters and the 6MWD. This study will provide important insights into the effectiveness of RT234 for improving exercise capacity in patients with PAH on stable background therapy.

## Methods

### Study design

This prospective, multi-center, open-label, two-cohort, dose-escalation, phase IIb trial in patients with PAH on ≤ 3 stable, disease-specific PAH background oral and/or inhaled therapies will evaluate the safety and efficacy of RT234 on exercise parameters. It is estimated that this trial will be conducted at up to 25 sites in the United States and Serbia. The trial began in September 2020 and is expected to be completed by early 2024. All CPET data collected during the trial will be transmitted electronically to a central facility, the CPET Core Laboratory, where they will be regularly reviewed. The trial will be conducted in accordance with the Declaration of Helsinki and the Good Clinical Practice Guidelines of the International Conference on Harmonisation, along with all local regulatory requirements. The informed consent document and the protocol have been or will be reviewed and approved by each investigator’s designated Institutional Review Board/Independent Ethics Committee, and by the sponsor. The trial is registered at ClinicalTrials.gov (identifier NCT04266197).

At each site, the investigator will obtain and document written informed consent for each patient and will determine the eligibility of patients before enrolling them in the trial. Patients will be divided into two successive cohorts, cohort 1 (receiving 0.5 mg RT234) and cohort 2 (receiving 1.0 mg RT234), with up to 86 patients in total. Each dose cohort will be further divided into two subgroups as defined by the number of background medications (i.e., up to two vs three). There will be up to 17 patients in each dose cohort using up to two background medications and up to 26 patients using three background medications. A Safety Monitoring Committee will independently review all safety and efficacy data from the trial once they have been collected. Data for patients who discontinue the study and provide an explanation will be summarized and listed.

### Study population

Each patient’s eligibility will be reviewed by the sponsor’s medical monitor before and after the baseline CPET. To be eligible for inclusion in the trial, patients must be between 18 and 80 years of age, inclusive; have a diagnosis of right heart catheterization–confirmed PAH with WHO/New York Heart Association functional class II–IV symptomatology; have a body mass index ≤ 35.9 kg m^–2^; be on stable PAH disease-specific background therapy of up to three oral and/or inhaled therapies; have a 6MWD of ≥ 150 m; and have minute ventilation (VE)/carbon dioxide production (VCO_2_) slope of ≥ 36 (Table 1). The sponsor’s chief medical officer or designated medical monitor must approve RT234 dosing. Patients will be excluded from the trial if they have baseline systemic hypotension, defined as mean arterial pressure < 50 mmHg or systolic blood pressure (SBP) < 90 mmHg, or a history of uncontrolled hypertension, defined as SBP > 175 mmHg or sitting diastolic blood pressure > 110 mmHg; use parenteral PAH medications; or have evidence or history of left-sided heart disease and/or clinically significant cardiac disease (Table 1).

**Table 1 Tab1:** Patient inclusion and exclusion criteria

**Inclusion criteria**
• ≥ 18 to ≤ 80 years of age
• BMI ≤ 35.9 kg m^–2^*
• Diagnosis of documented and RHC–confirmed PAH in any of the following: • Idiopathic, primary, or familial PAH ﻿ OR • PAH associated with connective tissue diseases OR • PAH associated with: HIV; simple, congenital systemic–to–pulmonary shunts ≥ 1-year post–surgical repair; exposure to drugs, chemicals, and toxins
• The patient must have had ventilation/perfusion scan, computerized tomography angiogram, or pulmonary arteriogram that rules out chronic thromboembolic pulmonary hypertension
• Previous PAH diagnosis with the following conditions: • Stable PAH without significant adjustments of disease–specific background PAH therapy ≥ 3 months before the CPET procedure AND • If on corticosteroids, has been receiving a stable dose of ≤ 20 mg per day of prednisone (or equivalent dose of other corticosteroid) for ≥ 30 days before the baseline CPET
• PFT within 6 months before commencement of screening, or during the screening period for this study, that fulfills the following: • FEV_1_ ≥ 60% predicted • FVC ≥ 60% predicted • FEV_1_/FVC ≥ 60%
• RHC performed and documented before screening that is consistent with the diagnosis of PAH, meeting all the following criteria: • mPAP ≥ 20 mmHg (at rest) AND • PCWP or LVEDP of ≤ 12 mmHg if PVR is ≥ 300 to < 500 dyn·s cm^– 5^, or PCWP or LVEDP ≤ 15 mmHg if PVR is ≥ 500 dyn·s cm^–5^ and, if PCWP is not available, then mLAP or LVEDP ≤ 15 mmHg or ≤ 12 mmHg in the absence of left atrial obstruction AND • PVR > 3 Wood units or > 240 dyn·s cm^–5^
• WHO/NYHA functional class II–IV symptomatology
• On stable^†^ PAH disease–specific background therapy of ≤ three oral therapies and/or inhaled therapy
• Able to walk ≥ 150 m on the 6MWT^‡^
• Has a VE/VCO_2_ slope ≥ 36 during the baseline CPET^§^
• Maximal effort on the baseline CPET must reach a peak RER of ≥ 1.0
• If the patient is taking the following concomitant medications, which may affect PAH, the patient must be on a stable therapeutic dose for ≥ 1 month before the screening, and the dosage must be maintained throughout the study: • Vasodilators • Digoxin • L–arginine supplement • Anticoagulants (anticoagulation status should be maintained/stable in the therapeutic range for ≥ 1 month before the screening)
**Exclusion criteria**
• Baseline systemic hypotension, defined as MAP < 50 mmHg or SBP < 90 mmHg at screening
• History of chronic uncontrolled asthma
• Patients who are unable or may find it difficult to use an inhaler device
• Requirement for intravenous inotropes within 30 days before the baseline CPET procedure
• Use of parenteral PAH medications
• Use of ricioguat as background PAH therapy ≤ 1 month before initiating screening or during the study through the end of visit 4
• Use of oral, topical, or inhaled nitrates within 2 weeks before the baseline CPET procedure
• Has history of or current uncontrolled systemic hypertension as evidenced by sitting SBP > 175 mmHg or sitting DBP > 110 mmHg at screening
• Portopulmonary hypertension, portal hypertension, or chronic liver disease determined to be Child–Pugh B or C
• Evidence or history of left–sided heart disease and/or clinically significant cardiac disease
• History of atrial septostomy
• History of known uncorrected right–to–left shunt; clinically relevant, persistent patent foramen ovale; or known Eisenmenger’s physiology
• Paroxysmal or uncontrolled atrial fibrillation
• Chronic renal insufficiency
• Serum alanine aminotransferase or aspartate aminotransferase that is ≥ 3x the upper limit of the normal range
• Platelets < 50,000 µL^–1^ at screening
• Hemoglobin concentration < 9 g dL^–1^ at screening

*6MWT* 6-minute walking test, *BMI* body mass index, *CPET* cardiopulmonary exercise testing, *DBP* diastolic blood pressure, *FEV*_*1*_ forced expiratory volume in 1 second, *FVC* forced expiratory vital capacity, *LVEDP* left ventricular end-diastolic pressure, *MAP* mean arterial pressure, *mLAP* mean left atrial pressure, *mPAP* mean pulmonary arterial pressure, *NYHA* New York Heart Association, *PAH* pulmonary arterial hypertension, *PCWP* pulmonary capillary wedge pressure, *PFT* pulmonary function testing, *PVR* pulmonary vascular resistance, *RER* respiratory exchange ratio, *RHC* right heart catheterization, *SBP* systolic blood pressure, *VE/VCO*_*2*_ ventilation/carbon dioxide production, *WHO* World Health Organization

*To consider individuals with BMI > 36 kg m^–2^, contact the sponsor Medical Director

^†^Stable is defined as no change in PAH-specific drug therapy within 3 months of screening visit 1 and for the duration of the study, and no change in dose of PAH-specific drug(s) within 1 month of screening

^‡^6MWT distance will be determined using the mean of the two 6MWT results done between visits 1 and 2, ≥ 2 hours apart if conducted on the same day, or ≥ 2 days apart

^§^As assessed by the CPET Core Laboratory

### Treatment protocol

Once patient eligibility has been confirmed, the study will begin with the screening visit(s) (visit 1), which will occur between 28 and 3 days before the CPET baseline visit (Fig. 2). The screening visit(s) will include two 6MWTs performed at least 2 days apart or, if tolerable to the patient, at least 2 hours apart on the same day (this will account for the learning effect associated with the 6MWT [14]; the relative difference between the two measurements must be ≤ 15%). The two screening 6MWDs will be averaged to determine the baseline 6MWD. At the CPET baseline visit (visit 2; day 1), enrolled patients will return to the testing center for pre-test assessments, CPET, and post-test assessments (Fig. 3). Eligible patients whose baseline CPETs are deemed evaluable by the CPET Core Laboratory will enter the treatment period (visits 3 and 4) for dosing with RT234 and post-dose CPET and 6MWT. At the CPET treatment visit (visit 3; day 8), patients will return to the testing facility for pre-CPET assessments and a single dose of RT234 (0.5 mg for cohort 1 and 1.0 mg for cohort 2), which will be administered with the aid of the study team. CPET will be performed 30 minutes post dose, at approximately the same time of day at each visit (within 2 hours), followed by post-test assessments. At the 6MWT treatment visit (visit 4; day 15), patients will undergo pre-6MWT assessments and receive a single dose of RT234. Patients will perform a 6MWT 30 minutes post dose and will then undergo post-test assessments. Plasma samples for PK analyses will be collected before and after RT234 dosing at visits 3 and 4. RT234 will only be administered to patients during visits 3 and 4 (Fig. 1); patients will not use RT234 outside these two visits. Patients will remain at the clinic for PK sampling and safety monitoring for 4 hours once all tests have been completed during visits 3 and 4, and safety monitoring will continue for 30 days after visit 4. Visit 5 (day 45 ± 3-day window) will involve a follow-up telephone call assessment of safety.

**Fig. 2 Fig2:**
[figure not shown]
Study design. Patients with pulmonary arterial hypertension will be assigned to two successive cohorts to receive one dose of RT234 (0.5 mg for cohort 1 and 1.0 mg for cohort 2) via the Dry Powder Inhaler (DPI; Plastiape S.p.A., Osnago, Italy). Screening 6-minute walking tests (6MWT) to determine baseline 6-minute walking distance will be conducted between days − 28 and − 3 of the study (visit 1). On day 1 (visit 2), patients will undergo baseline cardiopulmonary exercise testing (CPET) to measure peak oxygen consumption (VO_2_). On day 8 (visit 3), patients will receive 0.5 mg (cohort 1) or 1.0 mg (cohort 2) RT234 and will perform CPET 30 minutes post dose. On day 15 (visit 4), patients will receive 0.5 mg (cohort 1) or 1.0 mg (cohort 2) RT234 and will perform the 6MWT 30 minutes post dose. Blood samples will be collected at visits 3 and 4 before RT234 dosing; at 3, 15, and 30 minutes post dose; immediately at the end of the exercise period; and at 45, 75, 120, 180, and 240 minutes post dose for pharmacokinetic (PK) measurements. Patients will be monitored for 240 minutes post dose at visits 3 and 4. Follow-up will be conducted by telephone on day 45 (visit 5). Safety will be monitored throughout the study by the Safety Monitoring Committee (SMC)

### Outcome measures and endpoints

The primary efficacy endpoint is the change from baseline in peak oxygen consumption (VO_2_) measured during CPET performed 30 minutes after a single dose of 0.5 mg or 1.0 mg RT234. The secondary efficacy endpoints are change from baseline in 6MWD (mean of two 6MWDs at screening) to the 6MWD measured 30 minutes after RT234 dosing; change from baseline to post dose in the minute VE/VCO_2_ slope during CPET; change from baseline to post dose in the response of the partial pressure of end-tidal carbon dioxide apex to exercise (i.e., highest level during CPET); change from baseline to post dose in the duration of exercise during CPET; change from baseline to post dose in peak perceived dyspnea during CPET, as assessed by the Modified Borg Dyspnea Scale Score [15]; change from baseline to post dose in Patient Global Impression of Severity (PGI-S) for CPET (assessed before CPET and after a 2-minute cooldown after treadmill exercise while wearing mask, and then at 5-minute intervals [7, 12, and 17 minutes] without a mask); and changes from screening to post dose in PGI-S for 6MWT (assessed before the 6MWT and at 2 minutes after completion of the 6MWT).

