**Fig. 3 Fig3:**
[figure not shown]
Schedule of events. Study assessments will be performed over 45 days for each cohort. The schedule lists all the interventions, tests, and pre- and post-test assessments that will be performed at screening (days − 28 to − 3), cardiopulmonary exercise testing (CPET) at baseline (day 1), treatment (days 8 and 15), and safety follow-up (day 45) visits. Adverse event assessments and interval history reviews will be conducted at each visit. *6MWT* 6-minute walking test, *6MWD* 6-minute walking distance, *BP* blood pressure, *DASI* Duke Activity Status Index, *ECG* electrocardiogram, *HR* heart rate, *HRR* heart rate recovery, *NYHA* New York Heart Association, *O*_*2*_ oxygen, *PAH* pulmonary arterial hypertension, *PFT* pulmonary function testing, *PGI-S* Patient Global Impression of Severity, *PK* pharmacokinetic, *RPE* rating of perceived exertion, *SPO*_*2*_ peripheral oxygen saturation, *WHO* World Health Organization. *Potential patients will be screened approximately 3 days (≤ 28 days) before baseline CPET visit 2. ^†^Patients will be scheduled for treatment CPET visit 3, approximately 7 days after the baseline CPET visit 2. ^‡^If a patient prematurely discontinues the study any time before dosing or treatment CPET visit 3 because of an adverse event or patient safety concern, the patient should return to the clinic as soon as possible for an early termination study visit. ^§^Medical history will include a detailed PAH disease-specific medical history. ^II^Clinical laboratory tests may be repeated at the baseline CPET visit 2 if screening laboratory results are deemed clinically significant and warrant repeat testing. Clinical laboratory includes hematology, chemistry, and urinalysis. Prothrombin time international normalized ratio will also be tested in patients taking oral vitamin K antagonists. ^¶^Urine or serum pregnancy test at screening visit 1 required and a urine or serum pregnancy test at visit 3 and visit 4. **Either a single 0.5-mg dose (cohort 1) or a single 1.0-mg dose (cohort 2) of RT234 will be administered 30 minutes before CPET at visit 3 and 30 minutes before the 6MWT at visit 4. ^††^Interval history will include any signs, symptoms, or events experienced by the patient since the previous study visit. ^‡‡^Physical examinations at screening will be complete; all other physical examinations will be symptom directed. ^§§^Height will be obtained only at screening visit 1. ^II II^Resting vital signs (BP, HR, respiration rate, body temperature, and pulse oximetry [SPO_2_]) after resting for 5 minutes (sitting). Vital signs should be taken before any blood draw. BP, HR, and SPO_2_ will also be measured during CPET and into recovery (HR via continuous ECG monitoring during CPET and for 6 minutes post CPET, BP assessment every 2 minutes during CPET and for 6 minutes post CPET, and SPO_2_ assessment every minute during CPET and for 6 minutes post CPET) and at treatment 6MWT visit 4 (before RT234 dosing; 5 and 15 minutes post dose before 6MWT at 30 minutes post dose; and at 60 and 120 minutes post dose). ^¶¶^Continuous ECG monitoring will be collected during CPET and for 6 minutes post CPET. ***PFT may be completed at screening and/or baseline to confirm eligibility if historical PFT results within 6 months before screening are not available. ^†††^During the screening period, two 6MWTs will be performed at least 2 days apart, and the mean of the distance walked will be used for eligibility. If tolerable for the patient, the two 6MWTs at screening can be performed on the same day after a minimum of 2 hours between each test. The two screening 6MWDs must have a relative difference (i.e., [absolute difference between the two 6MWDs] / [mean of the two 6MWDs]) of ≤ 15%. If the difference is > 15%, a third 6MWT will be done during screening. If after the third 6MWT the relative distance is still > 15%, the Sponsor Medical Monitor will be contacted. The two longest 6MWDs will be averaged to determine the baseline 6MWD. ^‡‡‡^ The CPET assessments conducted at Visits 2 (pre dose) and 3 (post dose) will be conducted at approximately the same time of day (within 2 hours). ^§§§^PGI-S before CPET and at 2 minutes cool down off treadmill but still wearing the mask, then at 5-minute intervals: 7, 12, and 17 minutes with the mask off. For the 6MWT, PGI-S will be taken before and at 2 minutes after completion of the test. ^II II II^Modified Borg Dyspnea Scale assessment every minute during CPET and for 6 minutes post CPET. ^¶¶¶^Borg RPE Scale assessment every 2 minutes during CPET and for 6 minutes post CPET. ****Angina Scale assessment every 2 minutes during CPET and for either 6 minutes post CPET or, if indicated, until symptom recovery. ^††††^DASI assessment 10 minutes post CPET. ^‡‡‡‡^PK samples will be collected at visits 3 and 4 before RT234 dosing; at 3, 15, and 30 minutes post dose; immediately at the end of the exercise period; and at 45, 75, 120, 180, and 240 minutes post dose

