
The assessment of safety will involve evaluating the adverse event profile and acute physical and cardiac symptoms of single doses (0.5 or 1.0 mg) of RT234. The incidence and severity of TEAEs will be summarized by Medical Dictionary for Regulatory Activities (current version) System Organ Class and Preferred Term, National Cancer Institute Common Terminology Criteria for Adverse Events (current version) grade, and causality (attribution to study treatment and related/not related to investigational medicinal product). Changes in vital signs (blood pressure [BP], heart rate, respiratory rate, body temperature, and pulse oximetry) will be monitored, and physical examinations and 12-lead electrocardiograms (ECGs) will be conducted to measure the change from baseline to post dose.

Exploratory endpoints include the proportion of patients with improvement in risk category (low, intermediate, or high) for the VE/VCO_2_ slope criteria (defined in the 2015 European Society of Cardiology/European Respiratory Society Guidelines for the Diagnosis and Treatment of Pulmonary Hypertension [1]) during CPET from baseline to post dose, and changes in the following additional CPET parameters from baseline to post dose, according to the recommendations of the American Heart Association [16]: ECG response to exercise, VO_2_ at ventilatory threshold, change in respiratory exchange ratio at peak VO_2_, systolic BP response to exercise, pulse oximetry response to exercise, the non-peak Modified Borg Dyspnea Scale Score [15] throughout exercise (at every non-peak minute during CPET and for 6 minutes post CPET), the Borg Rating of Perceived Exertion Scale [17] throughout exercise (every 2 minutes during CPET and recovery), the Duke Activity Status Index [18] and the 4-Point Angina Scale [19].

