### Statistical analysis

The estimated total sample size is 86 enrolled patients, with a 5% dropout rate and a computed sample size of 17 and 26 patients with up to two and three background medications, respectively, per dose cohort (0.5 and 1.0 mg). This was derived using a one-sample two-sided *t* test (0.05 significance level and 80% power) to test the null hypothesis of no change in peak VO_2_ from baseline to post dose assessed during CPET performed 30 minutes after RT234 dosing. The assumed mean change from baseline is 1.5 and 1.2 mL O_2_·kg^–1^·min^–1^ [20] for patients with up to two and three background medications, respectively, in each dose cohort. A standard deviation of 2 mL O_2_·kg^–1^·min^–‍1^ is assumed for each dose cohort and background medication group.

The primary efficacy analysis will be conducted on the modified intention-to-treat (mITT) analysis set, which comprises all treated patients with baseline and post-baseline assessment of peak VO_2_. This mITT analysis set will serve as the basis for all efficacy analyses. The analysis procedure will be repeated for the per-protocol analysis set (all mITT patients who do not experience any major protocol violations) using a one-sample *t* test (if peak VO_2_ follows a normal distribution) to test the two-sided null hypothesis (0.05 significance level) of no change in peak VO_2_. The 95% CI for peak VO_2_ mean change will be derived from the *t* test if the normality assumption is not rejected. If it is rejected, a one-sample Wilcoxon signed-rank test will be used to determine the median change in peak VO_2_ with a 95% CI estimate.

The secondary efficacy analyses will be conducted on the mITT analysis set and will be repeated with the per-protocol analysis set, as described for the primary efficacy analyses. Because this study is exploratory (open-label, uncontrolled, and non-randomized) and its focus is on dose-escalation safety and activity, formal inferential statistics are not planned, and multiplicity adjustment will not be performed.

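### The VE/VCO2 slope on the visit 2 CPET is both the entry gate (at least 36) and the baseline for the slope endpoints, so zero change is not their no-effect value

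*Protocol article*

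**What the plan says.** All places are in the Methods of the protocol article.

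- **Gate.** Table 1 (inclusion criteria) requires that the patient "Has a VE/VCO_2_ slope ≥ 36 during the baseline CPET"; a footnote says the Core Laboratory assesses this. Under Study population, each patient's "eligibility will be reviewed by the sponsor’s medical monitor before and after the baseline CPET". Under Treatment protocol, "Eligible patients whose baseline CPETs are deemed evaluable by the CPET Core Laboratory will enter the treatment period (visits 3 and 4").
- **Baseline.** The Fig. 2 legend gives one pre-dose test: "On day 1 (visit 2), patients will undergo baseline cardiopulmonary exercise testing (CPET"). The Fig. 3 legend pairs it with the post-dose test at visit 3: "The CPET assessments conducted at Visits 2 (pre dose) and 3 (post dose"). No separate qualifying CPET and no repeat baseline CPET is described.
- **Endpoints.** Outcome measures and endpoints lists as secondary the "change from baseline to post dose in the minute VE/VCO_2_ slope during CPET", and as exploratory "the proportion of patients with improvement in risk category (low, intermediate, or high) for the VE/VCO_2_ slope criteria".
- **Analysis.** Statistical analysis specifies, for peak VO2, a one-sample t test or a Wilcoxon signed-rank test of no change at two-sided 0.05, with a 95% CI. The secondary endpoints are handled "as described for the primary efficacy analyses". The same section calls the study exploratory and uncontrolled, and says that formal inference is not planned.

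**The concern.** A single slope reading is the patient's true level plus test-to-test variation. A lower limit on that reading keeps patients whose value happened to be high on the day and turns away some whose value happened to be low. The visit 3 reading is not selected in this way, so its mean is expected to lie below the visit 2 mean even if RT234 does nothing. A lower slope reads as improvement, so the bias favours the drug.

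Without a control arm, nothing in the planned analysis separates this shift from a drug effect. Zero is then the wrong reference value, and the 95% CI for the change is centred in the wrong place. More patients would only tighten the interval around the biased value. The risk-category endpoint has the same exposure and, as defined, counts movement in the favourable direction only. The article says that the results will inform the design of phase III trials, where an overstated slope effect could mislead.

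**Working it through.** **The plan's own figure.** The article gives no sample size or variability for the slope; its calculation concerns peak VO2 and reproduces. For a one-sample two-sided t test at 0.05 with SD 2:

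- Change 1.5: n = 16 (power 80.1%); 16/0.95 = 16.8, so 17.
- Change 1.2: n = 24 (power 80.4%); 24/0.95 = 25.3, so 26.
- Total: 2 × (17 + 26) = 86, as stated.

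The evaluable subgroup sizes 16 and 24 are used below.

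**Inputs for the slope.** From the article: cut-off 36, one baseline test, one post-dose test, no control. Assumed, because the article gives none: pre-gate mean μ = 38 to 45, between-patient SD sb = 7 to 10, within-patient SD sw = 3 to 5, normal distributions, no drug effect.

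**Formula.** With st = √(sb² + sw²) and c = (36 − μ)/st, the expected change among patients who pass the gate is

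−(sw²/st) × φ(c)/(1 − Φ(c)).

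The test-retest correlation is r = sb²/st². The expression is negative whenever sw > 0, that is, whenever r < 1.

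**Middle case (μ = 40, sb = 8, sw = 4).**
- st = √80 = 8.944; r = 64/80 = 0.80; c = −4/8.944 = −0.447.
- φ(c)/(1 − Φ(c)) = 0.361/0.673 = 0.537.
- Change = −(16/8.944) × 0.537 = −0.96 units.

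**Range.** Rejection rates are for the nominal 5% two-sided one-sample t test, by simulation with no drug effect.

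| μ, sb, sw | r | Null change | Rejects, n = 16 | Rejects, n = 24 |
|---|---|---|---|---|
| 38, 7, 5 | 0.66 | −(25/8.602) × 0.656 = −1.91 | 18–19% | 26–27% |
| 40, 8, 4 | 0.80 | −0.96 | 10% | 13% |
| 45, 7, 3 | 0.84 | −(9/7.616) × 0.225 = −0.27 | 5–6% | 6% |
| 45, 8, 2 (outside the range) | 0.94 | −(4/8.246) × 0.255 = −0.12 | 5% | 6% |

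A second set of assumptions (μ 36 to 48, total SD 8 to 10, r 0.70 to 0.95) gives −0.06 to −2.4 units, negative in every scenario. If the qualifying test were separate from the baseline test, the expected null change under the same model would be 0.

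**Can the shift be corrected?** Regress the post-dose slope on the baseline slope in treated patients, evaluate the line at the mean of all baseline CPETs including gate failures, and subtract that mean. In the middle case, with 16 + 24 = 40 treated in one dose cohort, the bias falls from about −0.96 to about −0.03 and the standard error rises from 0.88 to 1.12 (27%). At μ = 38, sb = 8, sw = 4, it rises from 0.87 to 1.26 (45%); at μ = 45 with the same SDs, from 0.86 to 0.94 (9%). With strongly right-skewed true slopes (exponential shape, mean 40, SD 8, sw = 4), the raw bias of −1.49 only shrinks to about −1.25.

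**The case against.** The strongest reply is that little depends on this. The slope change is one of several secondary endpoints and the risk category is exploratory. Neither the primary endpoint nor the sample size rests on them. The article disclaims formal inference, and its Discussion admits that the open-label design without placebo raises the risk of bias. Every slope input above is assumed, and the highest rejection rates come from one corner with r = 0.66.

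Most of this stands and limits the severity. It does not remove the point. The same Statistical analysis section specifies tests of no change with 95% CIs and extends that approach to the secondary endpoints; the estimate is biased whatever the test is called. The general caveat about bias does not mention selection on the baseline value. Nor can the matter simply be left to an analysis plan, because the entry rule and the endpoint definition are both fixed here, and an ordinary change-from-baseline analysis would carry the bias forward.

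Three stronger readings are tempting but unsupported:

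- **That the peak VO2 result is biased in the same way.** Peak VO2 has no entry cut-off. It could be affected only indirectly, through its correlation with the slope.
- **That the share of patients falling below 36 on retest would be counted as improved in risk category.** The article takes the category limits from an outside guideline and does not state them, so no figure can be given.
- **That comparing 1.0 mg with 0.5 mg removes the bias.** The cohorts are sequential and not randomised. The bias cancels only if their pre-gate slope distributions are similar, and the contrast does not compare drug with no drug.

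**Conclusion.** The point holds at moderate severity. One visit 2 CPET serves as both gate and baseline for the two VE/VCO2 endpoints, and with no control arm zero is not the no-effect value for the change in slope. The direction, an apparent improvement, is certain if test-retest correlation is below 1.

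The size is not derivable from the article. Under the assumed range it is about −0.3 to −1.9 units, with a nominal 5% test rejecting in about 5% to 27% per background subgroup (n = 16 to 24). It is close to nil if most screened patients lie well above 36 and repeatability is high. A reader might infer that any observed fall in slope would be an artefact; the article does not support that, because the shift could be small beside a real effect.

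**What to change.** 1. For VE/VCO2 slope, do not test or interpret the change against zero. Report the raw change as descriptive, and state that it includes the effect of selection on the baseline value.
2. Add, as a sensitivity analysis, the regression-to-the-mean-corrected change described above, using all baseline CPETs read by the Core Laboratory, including those that failed the gate. State its linearity and normality assumptions, and show the pre-gate slope distribution so that readers can judge both the likely size of the bias and the fit of the correction.
3. For the risk-category endpoint, report the proportion worsened as well as improved.
4. The 1.0 mg versus 0.5 mg contrast may be shown, with the condition that the two cohorts' pre-gate slope distributions are similar.

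Cost: changed analysis wording and a little extra analysis, with no new visits or patients. The corrected estimate has a standard error larger by roughly 10% to 50%, depending on how close the pre-gate mean is to 36. It also refers to a population that includes patients who failed the gate, and it can leave most of the bias in place under strong skew. For these reasons it should be a sensitivity analysis and not the main result.
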